### **9.7.1 Period of pregnancy information collection**

Any pregnancies that occur from the first dose of the study product to 30 days after the last dose will be reported in the appropriate form. If a pregnancy is determined more than 30 days after the last dose, the investigator may report it based on his/her clinical judgment.

### **9.7.2 Measures to be taken if pregnancy occurs**

If a female patient becomes pregnant while participating in the study, the investigator must be notified immediately, and recommend that she immediately discontinue the study treatment. Pregnancy information should be collected and recorded in an appropriate form and submitted to the sponsor's pharmacovigilance team by the investigator within 24 hours of learning of the patient's pregnancy. The investigator should consult with the patient to discuss the risks of continuing the pregnancy and the possible effects on the fetus, and if the patient insists on continuing the pregnancy, the patient and the fetus should continue to be monitored until the outcome of the pregnancy is determined. Maternal and infant information should all be provided to the sponsor. In general, the follow-up will end within 6-8 weeks after the expected date of delivery. Any early termination of pregnancy should be reported.

[figure not shown]

Pregnancy itself is not regarded as an AE unless the study drug may have interfered with the effectiveness of a contraceptive medication. Extrauterine pregnancy and pregnancy resulting in congenital anomalies/birth defects, spontaneous abortion or severe complications will be reported as SAEs.

#### **9.7.3 Measures to be taken if a male patient's female partner becomes pregnant**

The investigator will attempt to collect pregnancy information of any pregnant female partner during male subject's participation in this study. The pregnancy should be recorded in an appropriate form and submitted to the sponsor by the investigator within 24 hours of learning of the partner's pregnancy. The partner will be followed up to determine the outcome of the pregnancy. Maternal and infant information should all be provided to the sponsor. In general, the follow-up will end within 6-8 weeks after the expected date of delivery. Any early termination of pregnancy should be reported.

#### **9.7.4 Warnings and precautions for use**

At the time the study protocol passes review, there is no evidence of other special warnings or precautions for use other than those covered in the Investigator's Brochure. Additional safety information collected between IB updates will be communicated in the form of an investigator circular. This information will be incorporated into the patient's ICF and, if needed, should be discussed with the patient during the study.

[figure not shown]

## 10 Statistical Analysis

### 10.1 Sample Size Calculation

In the HQP1351 SJ-0002 CML patient study, the MTD has been determined to be 50 mg. But starting from the 12 mg dose group, the drug has shown its efficacy. The study is being expanded at 30 mg, 40 mg and 50 mg to determine the dose groups with the best efficacy/safety ratio. According to the data of HQP1351 SJ-0002 CML patient study, this study has been modified accordingly to randomize subjects into the 30 mg, 40 mg and 50 mg dose groups at the same time, about 10 subjects each.

As of February 2021, HQP1351 has undergone a total of 9 clinical studies, and preliminary results from the Phase I and Phase II clinical trials that have been conducted show a favorable safety profile in the dose range of 50 mg QOD. HQP1351 (olverembatinib tablets) has been granted conditional marketing authorization from the National Medical Products Administration on November 24, 2021, with a recommended dose of 40 mg QOD. Based on the safety data from 9 clinical studies that are conducted with HQP1351 and the safety and efficacy data of 36 patients already enrolled in this study, 40 mg QOD is selected as the dosage for adult subjects after discussion between the investigator and the sponsor. After the randomization of subjects at 30 mg, 40 mg and 50 mg QOD, with about 10 subjects in each group, it is planned to enroll 10-20 subjects in the non-randomized part to further explore the safety and efficacy of the drug, and the final number of enrolled subjects will be determined after discussion between the investigator and the sponsor according to the situation.

### 10.2 Study Endpoints

#### 10.2.1 Primary endpoints

Safety and tolerability assessments include AEs, SAEs, physical examination, vital signs, ECG, and clinical laboratory tests.

#### 10.2.2 Secondary endpoints

Secondary endpoints include the PK profile of HQP1351 in vivo, and efficacy of HQP1351 in the treatment of gastrointestinal stromal tumors.

#### Definition of efficacy:

**Objective response rate (ORR):** Defined as the percentage of subjects with confirmed best overall response of complete response (CR) and partial response (PR) (evaluated as per RECIST v1.1 by the investigator).

- When calculating ORR, PR and CR confirmed prior to any other antitumor therapy should both be counted as responses, regardless of how many assessments are missing prior to response.
- According to RECIST v1.1, patients whose best overall response is “unknown” or “not evaluated” will be considered as non-responders for ORR estimation.

[figure not shown]

- Patients who develop PD and continue to receive the study treatment after PD will be considered to have PD at the time the progression is determined, and will be counted for PD and regarded as non-responders for ORR and other efficacy calculations.

**Clinical benefit rate (CBR):** Defined as the proportion of patients with a complete response (CR), partial response (PR), and stable disease (SD) for  $\geq 16$  weeks.

**Duration of response (DOR):** In patients with a response (PR or CR) (as per RECIST v1.1), DOR is defined as the time between the date of the first documented response (PR or CR) and the date of the first documented PD or the date of death from any cause. The censoring rules for DOR are the same as the following censoring rules for PFS.

**Progression-free survival (PFS):** Defined as the time between the date of the first dose of HQP1351 and the date of the first documented PD (as per RECIST v1.1) or the date of death from any cause.

Patients who do not have PD or death as of the analysis cutoff date, or who do not have PD when starting any further antitumor therapy, will be censored at the last adequate tumor assessment prior to the cutoff date, or prior to the date of antitumor therapy.

**Overall survival (OS):** Defined as the time interval from the first dose of HQP1351 to death due to any reason.

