The study is initially designed as a Phase I study with standard 3+3 dose escalation. Based on the study results of HQP1351 SJ-0002 in CML patients and the consensus reached at the SJ-0003 kick-off meeting with the investigator, this study will explore the safety in the 30 mg, 40 mg, and 50 mg dose groups in parallel, and 10 subjects will be enrolled by means of randomization at each dose level using the IWRS. After preliminary adult data are available, adolescent subjects with advanced and/or metastatic wild-type GIST will be included. The dosage for adolescents is based on the adult dose and the selected dose will be adjusted according to their body weight. If the subject's body weight is  $\geq 40$  kg, the dose of 40 mg QOD will be given based on the adult dose. If the subject's body weight is  $\geq 30$  kg and  $< 40$  kg, the dose of 30 mg QOD will be given. If the subject's body weight is  $\geq 20$  kg and  $< 30$  kg, 20 mg QOD will be given. Based on the safety data from 9 clinical studies that have been conducted with HQP1351 and the safety and efficacy data of 36 patients already enrolled in this study, 40 mg QOD is selected as the dosage for non-randomized adult subjects after discussion between the investigator and the sponsor.

HQP1351 tablets will be administered orally to eligible subjects once every 2 days in a 28-day cycle. Subjects will receive treatment until PD, intolerable toxicity, death, or termination of treatment for any other reason. If a subject is assessed to have PD according to the RECIST v1.1 criteria, but the investigator determines that the subject will benefit from continuing the

[figure not shown]

study, then the subject may continue to take HQP1351 and undergo safety follow-up yet no more efficacy follow-up after PD is documented. During medication, subjects will not receive other antitumor study drugs, marketed drugs, or treatment methods other than HQP1351. Symptomatic (including those directed at controlling symptoms resulting from the patient's malignancy) and supportive treatments are allowed.

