### **8.1.9.3 Best overall response: all time points**

The best overall response is determined once all the data for the patient is known. The best overall response of the study is defined as the best response across all time points (for example, a patient who has SD at first assessment, PR at second assessment, and PD on last assessment has a best overall response of PR). When SD is believed to be best response, it must also meet the protocol specified minimum time from baseline. If the minimum time is not met when SD is otherwise the best time point response, the patient's best response depends on the subsequent assessments. a patient who has SD at first assessment, PD at second and does not meet minimum duration for SD, will have a best response of PD. The same patient lost to follow-up after the first SD assessment would be considered not evaluable.

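### The third ORR bullet in section 10.2.2 turns a confirmed responder who is kept on drug after progression into a non-responder, against the protocol's other response rules

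*Protocol*

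**What the plan says.** Section 10.2.2 (Definition of efficacy) rests ORR on confirmed best overall response by RECIST v1.1 and adds three bullets. The first says that "PR and CR confirmed prior to any other antitumor therapy should both be counted as responses". The third deals with patients who progress and stay on HQP1351. It fixes their PD at the date progression is established, then says that they "will be counted for PD and regarded as non-responders for ORR and other efficacy calculations". It makes no distinction between patients with and without a response confirmed before the progression.

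Two other provisions bear on the same patient:

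- Section 8.1.9.3 gives a worked case: "a patient who has SD at first assessment, PR at second assessment, and PD on last assessment has a best overall response of PR".
- In section 10.2.2, "DOR is defined as the time between the date of the first documented response (PR or CR) and the date of the first documented PD"; death also ends it, and it is calculated in patients with a response.

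Section 4.1 (and the Synopsis) allows treatment beyond progression. If the investigator judges that the patient will benefit, "the subject may continue to take HQP1351 and undergo safety follow-up", but efficacy follow-up ends once PD is documented.

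**The concern.** The third bullet is triggered by a treatment decision made after the response has come and gone. Whether a patient responded is settled by scans taken before PD; whether the patient then stays on drug is a later judgement by an investigator in an open-label trial. If the bullet is followed as written, ORR mixes the two, and a site that more often treats beyond progression reports a lower response rate for the same scans.

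The phrase about other efficacy calculations carries the rule into CBR and into the set of patients in whom DOR is estimated. PFS is not affected, because PD is dated when it is determined in either case.

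Only the protocol is at hand, and a statistical analysis plan may exist. This is still not a detail left to that plan: the protocol states a rule that a later plan would have to overrule.

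**Working it through.** **Step 1. The provisions side by side.** Take patients A and B, each with SD, then PR, then a confirmed PR, then PD. Neither receives other antitumour therapy. A stops HQP1351 at PD; B continues.

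| Provision | A (stops) | B (continues) |
|---|---|---|
| ORR by confirmed best overall response (10.2.2), with the example in 8.1.9.3 | responder | responder |
| First ORR bullet (10.2.2) | responder | responder |
| DOR definition (10.2.2) | included, event at PD | included, event at PD |
| Third ORR bullet (10.2.2) | not covered, so stays a responder | non-responder |

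Continued HQP1351 is not another antitumour therapy, so the first bullet does not exclude B. Only the third bullet separates the two, and only by the decision to continue.

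**Step 2. Size for ORR.** The protocol gives no ORR target or precision figure, so there is nothing to reproduce. Let p be the true confirmed ORR, f the share of responders with PD by the analysis, and c the share of those kept on drug. None of the three is in the protocol; all are assumptions. Under the literal rule:

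expected ORR = p × (1 − f × c)

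For p = 20%:

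| | c = 0.1 | c = 0.3 | c = 0.5 | c = 0.8 |
|---|---|---|---|---|
| f = 0.5 | 19.0% | 17.0% | 15.0% | 12.0% |
| f = 0.8 | 18.4% | 15.2% | 12.0% | 7.2% |

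The corners are 0.20 × (1 − 0.05) = 0.190 and 0.20 × (1 − 0.64) = 0.072. The factor 1 − f × c never exceeds 1, so the error in ORR is never upward. The factor does not depend on p: with p = 10% the same corners are 9.5% and 3.6%, and with p = 30% they are 28.5% and 10.8%.

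**Step 3. The same in counts**, with exact binomial 95% intervals as section 10.4.2 prescribes:

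- Assumed 12 responders in 60 (the upper end of the planned 50-60 subjects): 12/60 = 20.0% (10.8 to 32.3). If half are recounted: 6/60 = 10.0% (3.8 to 20.5).
- Wild-type GIST, where section 1.6 reports 1 PR in 6: 1/6 = 16.7% (0.4 to 64.1). If that responder were to progress and stay on drug: 0/6 = 0% (0 to 45.9). Section 1.6 does not say that this happened; the patient was still in PR at Cycle 13.

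**Step 4. Direction for DOR.** The patients removed all have a DOR event (PD), while censored responders stay in. A simulation with an exponential DOR of median 8 months (all settings assumed) gave these Kaplan-Meier medians:

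- Censoring uniform over 0-24 months (58% events), continuation unrelated to DOR: 8.0 months without the rule; 8.4, 9.6 and 12.0 months at c = 0.1, 0.3 and 0.5; not reached at c = 0.8.
- No censoring, continuation unrelated to DOR: about 8.0 months, unchanged.
- No censoring, responders with DOR above 8 months kept on drug more often (0.6 against 0.2): 5.4 months. In the reverse case: 11.3 months.

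The DOR estimate therefore depends on the decision to continue, but the sign of the bias is not determined.

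**The case against.** The strongest defence is that the bullet was never meant to undo an earlier response. Its opening words fix PD at the time it is determined, which can be read as giving no credit for shrinkage seen during treatment beyond PD. The ORR definition, the first bullet, section 8.1.9.3 and the DOR definition all keep the responder, so a careful analyst might follow them. This stands in part: the text does not settle which rule governs, and the firm finding is the contradiction, not that responders will in fact be recounted. It does not rescue the bullet, which states no such limit. Efficacy follow-up already ends at PD, so on that reading the bullet does little. It is not quite idle, since section 8.1.9 runs best overall response to EOT and section 7.6 lists imaging at EOT, but that purpose needs only a rule about scans after PD.

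A reader might infer more in two respects, and the documents do not support either:

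- *That DOR is biased downward like ORR.* With censored responders present and continuation unrelated to DOR, the simulated bias is upward; a downward shift appeared only when longer responders were preferentially kept on drug.
- *That nearly every responder is exposed, because section 4.4 places the final analysis after subjects have left the study.* Leaving may be for PD or for other reasons, and the bullet also needs treatment after PD. By default treatment ends at PD (sections 3.3.1 and 4.1); continuation is an exception at the investigator's judgement, and no rate is given.

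It is also fair that ORR carries no hypothesis test or decision threshold, that the primary endpoint is safety, and that all efficacy data will be listed, so an affected patient could be found and recounted.

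**Conclusion.** The concern holds as an internal contradiction in a stated rule. Section 10.2.2 gives two opposite ORR classifications for a patient with a confirmed CR or PR who later progresses and stays on HQP1351. Following the third bullet literally can only lower ORR, can lower CBR, and makes membership of the DOR set depend on the same post-progression decision, with no fixed direction of bias.

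The size cannot be fixed from the protocol. For an assumed true ORR of 20% it runs from a loss of 1.0 percentage point (20% to 19.0%) to a loss of 12.8 points (20% to 7.2%), depending on the assumed shares who progress and continue.

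The severity is moderate. A reader might think the point decisive for the trial, but ORR is a secondary, descriptive endpoint. It still matters, because sections 4.4 and 10.4 bring efficacy into the RP2D choice and responses look few: none among the 28 GIST subjects with an efficacy assessment in section 1.5 (10 SD, 18 PD), and 1 PR in 6 wild-type subjects in section 1.6. One or two recounted patients would show.

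**What to change.** Replace the third ORR bullet in section 10.2.2 with:

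> PD is dated at its first documentation; assessments after PD do not contribute to best overall response; a CR/PR confirmed before that PD remains a response for ORR, CBR and DOR whether or not treatment continues after PD.

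This keeps the bullet's plausible purpose (no credit for scans after PD) and agrees with the first bullet, section 8.1.9.3 and the DOR definition. Under it, ORR stays at p in the formula above for any f and c.

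The cost is one sentence in the protocol, repeated in the statistical analysis plan, with no new data and no change to visits or treatment. It should be settled before the final analysis, so that the choice of rule is not made with the responders known.

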### 10.2.3 Exploratory endpoints

Mutations and/or expression profiles of KIT, PDGFRa or other and other tumor-associated genes associated with the efficacy of HQP1351.

## 10.3 Analysis Sets

### Full analysis set (FAS)

The FAS includes patients who have received at least one dose of HQP1351 and have baseline tumor assessment data.

### Per-protocol set (PPS)

The PPS consists of a subset of patients in the FAS who meet the requirements of the clinical study protocol. The PPS includes patients with adequate tumor assessment at baseline and follow-up tumor assessment  $> 2$  weeks after initiation of treatment (unless PD has been previously observed), and no major protocol violations.

Patients with major protocol violations will be excluded from the PPS, and protocol violations leading to exclusion from the PPS will be defined in detail in the Statistical Analysis Plan.

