## **1.5 HQP1351 Clinical Overview**

As of February 2021, HQP1351 has undergone a total of 9 clinical studies, including 3 Phase I studies (SJ-0002, SJ-0003 and HQP1351CU101), 3 clinical pharmacology studies [HQP1351LC104, HQP1351XC105 and HQP1351XC106 (in healthy volunteers)] and 3 Phase II pivotal studies (HQP1351CC201, HQP1351CC202 and HQP1351CC203). All studies were conducted in China except for HQP1351CU101 and HQP1351XC106 which were conducted in the United States. The Phase I clinical study of HQP1351 for GIST (SJ-0003) is ongoing in Chinese mainland. A total of 36 GIST subjects were enrolled as of January 31, 2021, and treated with HQP1351 orally QOD in 4 dose groups: 3 in the 20 mg dose group, 11 in the 30 mg dose group, 11 in the 40 mg dose group, and 11 in the 50 mg dose group, in 28-day cycles. All subjects were TKI-resistant GIST subjects who had previously been heavily treated. The Phase I study is currently actively enrolling subjects. Of the 36 GIST subjects, 28 have completed at least one efficacy assessment. The results are as follows: 10 subjects had stable disease (SD) and 18 subjects had progressive disease (PD).

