Safety data were obtained from a total of 269 CML patients in 5 CML studies with safety and efficacy as primary or secondary endpoints. The data cutoff date for SJ-0002, CC201, and CC202 was 12 months after enrollment of the last patient; the data cutoff dates for CC203 and CU101 were May 25, 2021, and January 31, 2021, respectively. The mean treatment period of study drug was 13.1 (range: 0.2; 38.9) months. Approximately 99% of subjects experienced at least one treatment-emergent adverse event (TEAE), and most TEAEs were mild or moderate and could be resolved with or without interruption, dose reduction, or discontinuation of the study drug. The most common TEAEs ( $\geq 20\%$ ) included hematological abnormalities (reduced platelet count, white blood cell count decreased/neutrophil count decreased, and anemia), skin pigmentation, liver function test abnormal (ALT increased, AST increased, GGT increased, or blood bilirubin increased), metabolic disorder (hypertriglyceridemia, hypocalcemia), and others (pyrexia, proteinuria and blood creatine phosphokinase increased). 10% of patients withdrew from the study due to AEs. 26% of patients experienced SAEs, but no deaths due to AEs were reported. Based on the safety profile of HQP1351 in CML, reduced platelet count and anemia were the most frequently reported SAEs related to the study drug, and were identified as important risks of HQP1351 in the treatment of CML patients. Based on available data, HQP1351 is well tolerated in CML patients and has a positive benefit/risk ratio for CML patients who are resistant or intolerant to multiple TKIs. Data were obtained from 36 GIST subjects in the SJ-0003 study, including 3, 11, 11, and 11 subjects enrolled in 4 designated dose cohorts (20 mg QOD, 30 mg QOD, 40 mg QOD, and 50 mg QOD), and the safety analysis was based on a combination of the 4 dose groups. As of January 31, 2021, the mean duration of treatment for GIST patients was 2.5 (range 0.1-13.1 months) months. All subjects (100%) experienced at least one TEAE, and most TEAEs were mild or moderate and could be resolved or recovered with or without interruption, dose reduction, or discontinuation of the study drug. Among them, 5 (14%) subjects discontinued treatment due to AEs. The most common hematological AEs ( $\geq 20\%$  TEAEs) in GIST subjects included white blood cell count increased (63.9%), neutrophil count increased (52.8%), and anemia (41.7%). The most common non-hematological AEs ( $\geq 20\%$  TEAEs) included constipation (44.4%), asthma (38.9%), aspartate

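### The per-protocol set excuses a missing follow-up scan for earlier PD but not for death, so the supportive PPS efficacy estimates leave out early deaths

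*Protocol*

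**What the plan says.** - **PPS (Section 10.3).** The PPS is a subset of the FAS. It needs an adequate baseline assessment and a follow-up tumor assessment more than 2 "weeks after initiation of treatment (unless PD has been previously observed), and no major protocol violations". The section leaves to the SAP only the list of violations that lead to exclusion. The scan condition and its single exception are settled in the protocol.
- **FAS (Section 10.3).** One dose and a baseline tumor assessment suffice. No post-baseline scan is needed.
- **Roles (Section 10.4.2).** All efficacy analyses use the FAS. The PPS is supporting.
- **ORR (Section 10.2.2).** Subjects whose best response is unknown or not evaluated "will be considered as non-responders for ORR estimation".
- **CBR (Section 10.2.2).** The proportion of patients with CR, PR, or SD lasting at least 16 weeks. There is no separate sentence on subjects who cannot be evaluated.
- **PFS (Section 10.2.2).** Time runs from first dose to PD or death from any cause. Subjects with neither at the cutoff "will be censored at the last adequate tumor assessment prior to the cutoff date"; those who start other antitumor therapy without PD are censored at the last adequate assessment before it.
- **Scan timing (Sections 7.5.1, 7.6, 7.7.2.1 and 8).** Scans are due every 8 weeks and at end of treatment, unless imaging is recent. They continue every 8 weeks after treatment stops before PD.
- **Data so far (Section 1.5).** "A total of 36 GIST subjects were enrolled as of January 31, 2021". "Of the 36 GIST subjects, 28 have completed at least one efficacy assessment": 10 with SD and 18 with PD. Section 1.5.2 reports fatal AEs in 4 subjects (11%).

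**The concern.** The exception for PD shows the intent: a subject who has already failed should not drop out of the PPS merely because no later scan exists. Death before the first scan is also a failure under the protocol's own PFS definition, yet it is not excepted. The same subject is therefore an event in one analysis and missing from the other.

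The PPS estimates are thus conditional on surviving to a scan or to documented PD. A supporting analysis is meant to show whether the FAS result is robust. One that removes early deaths, and so can move in only one direction on this account, is weak evidence of that. The groups are small, about 10 subjects per randomized dose (Section 10.1), so one exclusion in a group of 10 multiplies a rate by 10/9 = 1.11.

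**Working it through.** **1. One subject under each rule.** Take a subject who has a baseline scan, receives study drug, and dies before any follow-up scan without documented PD.

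| Quantity | FAS | PPS as written |
|---|---|---|
| ORR | in denominator, non-responder | excluded |
| CBR | in denominator, cannot enter numerator | excluded |
| PFS | event at date of death | excluded |

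The subject adds nothing to the ORR or CBR numerator and one event to PFS. Leaving the subject out therefore cannot lower any of the three estimates.

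**2. The protocol's counts, reproduced.** Enrolled: 3 + 11 + 11 + 11 = 36. Assessed: 10 + 18 = 28. Not assessed: 36 − 28 = 8 (22.2%). Fatal AEs: 4/36 = 11.1%, stated as 11%. All agree.

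**3. Effect of the exception on disease control.** Assume that the PPS at that cutoff is the 28 assessed subjects (no other exclusions), and let d be the number of fatal cases that were unscanned and without observed PD. The protocol does not give d, so it runs from 0 to 4. With death excepted, the rate is 10/(28 + d):

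| d | Rate with death excepted |
|---|---|
| 0 | 10/28 = 35.7% |
| 1 | 10/29 = 34.5% |
| 2 | 10/30 = 33.3% |
| 3 | 10/31 = 32.3% |
| 4 | 10/32 = 31.3% |

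The largest change is 35.71 − 31.25 = 4.46 points, a factor of 32/28 = 1.14. Exact 95% intervals are 18.6 to 55.9% for 10/28 and 16.1 to 50.0% for 10/32. SD durations are not reported, so this is any-SD disease control, an upper bound on the protocol's CBR.

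**4. ORR.** There were no responders among the 28. The estimate is 0% either way; the upper exact limit is 12.3% for 0/28 and 10.9% for 0/32.

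**5. PFS at week 8.** Assume that all 18 PDs fall at the first scan, all 10 SD subjects pass it, and unscanned subjects who did not die leave the risk set at or before first dose. With d = 4, Kaplan-Meier gives 10/32 = 31.3% in the FAS and 10/28 = 35.7% in the PPS as written. Excepting death brings the PPS figure to 31.3%.

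**6. PFS censoring and CBR wording.** If the only adequate scan is the baseline one, up to 28 days before first dose (Section 8), an event-free subject gets a censoring date before time zero. Moving that date to Day 1 leaves the Kaplan-Meier curve unchanged unless an event falls on Day 1, because the subject is in no later risk set. For CBR, a subject with no scan cannot be in the numerator and stays in the FAS denominator, so the status is already determined.

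**The case against.** The strongest reply is that this is a supporting set in a Phase I trial whose primary endpoint is safety. The FAS governs every efficacy analysis and keeps these subjects, and limiting a per-protocol set to subjects evaluable for response is a common choice. That stands as to consequence: no main result changes. It does not explain why PD is excepted and death is not, when both are PFS events.

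A second reply is that many early leavers will have a follow-up scan, at end of treatment or at the 8-weekly visits after stopping. That is fair for subjects who stop alive. It does not help those who die first.

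A reader might also infer something stronger: that 8 of 36 subjects left before a scan, and that efficacy is overstated by the gap between 10/28 (35.7%) and 10/36 (27.8%), which is 7.9 points. The documents do not support this. Section 1.5 says "The Phase I study is currently actively enrolling subjects", and Section 1.5.2 says "the mean duration of treatment for GIST patients was 2.5 (range 0.1-13.1 months) months", so some of the 8 may simply not have reached their first scan. Section 1.5 gives counts and calculates no rate on 28. The overlap between the 8 and the 4 fatal cases is not stated, and one fatal case was attributed to PD, so the existing exception may already cover it.

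**Conclusion.** The point holds for the PPS only. As written, the definition drops subjects who die before any follow-up scan without observed PD, and this shifts the supportive ORR, CBR and PFS upward or not at all. In the January 2021 data the shift in any-SD disease control lies between 0 and about 4.5 points. The upper end requires all four fatal cases to have been unscanned and without observed PD.

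It does not follow that efficacy results in general are inflated. The FAS is primary for efficacy and needs no post-baseline scan. The ORR rule for subjects not evaluated is conservative. CBR status follows from its definition on the FAS. The PFS censoring date is an untidy definition with essentially no effect on the curve. DOR needs no extra rule, since every responder has a post-baseline scan.

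**What to change.** In Section 10.3, change the PPS exception to read: *unless PD or death has previously occurred*. This is a two-word addition plus a change of verb. It needs no new data, and its only cost is that the supportive PPS rates may become slightly less favourable.

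Two optional clarifications in Section 10.2.2, or in the SAP if it does not already contain them, would have no material effect on the estimates:

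- PFS is censored at Day 1 when there is no post-baseline assessment and no death.
- Subjects who cannot be evaluated count as having no clinical benefit for CBR.
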